#### Sample size

The sample size was calculated using the approach proposed by Frison and Pocock [19]. The calculation is based on the comparison between the two study arms of the mean of 4 post-treatment measurements during the 1st year of follow-up (at 3, 6, 9 and 12 months). Assuming a standard deviation of 2 points of HbA1c, a correlation of 0.4 between the pre- and post-randomization measurements, and a correlation of 0.5 between the post-randomization measurements, 117 patients are required per arm (234 patients in all) to detect a difference of 0.5 points of HbA1c with a power of 80%, a two-sided type I error of 5%. This calculation was computed using Stata SE 11.2 software. To avoid any loss of power due to patients lost to follow-up, the cohort obtained is increased by 20% to give a total of 282 patients to be enrolled (141 per arm).

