#### Allocation

Randomization was based on a 1:1 ratio and stratified on the baseline HbA1c level (<7.5% vs ≥7.5%). The allocation sequence was randomly permuted in blocks of varying size (2, 4 or 6), generated by computer (Stata SE 11.2, ralloc procedure) by the methodologist. There was no blinding procedure in this open-label trial, however randomization was centralized at the Toulouse University Hospital and managed by the project manager and the two clinical research associates, and the allocation sequence was unknown to the investigators who enrolled participants.

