##### Primary outcome analysis

The primary outcome (difference between HbA1c level after 1 year of follow-up and baseline targeted HbA1c level) will be compared between the two groups. The difference between the the intervention and control groups will be assessed firstly using bivariate analysis (Student’s T test), and secondly using mixed model analysis for repeated measures. The mixed model will be adjusted for the baseline value of HbA1c, as well as additional baseline variables that might be potential confounders: center, age, gender, treatment by insulin, duration of diabetes and history of diabetes complications. To manage missing data, a sensitivity analysis using the last observation carried forward (LOCF) technique will be applied. Secondary outcomes will be analyzed according to the same principles. A bivariate analysis will be computed, followed by a multivariate analysis of covariance (ANCOVA) adjusted for the baseline value of the corresponding secondary outcome and the same set of potential baseline confounders than in the primary outcome analysis.

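### The secondary-outcome ANCOVA, as worded, omits baseline HbA1c, the variable on which randomisation was stratified; for outcomes that HbA1c predicts, standard errors come out somewhat too wide

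*Protocol article*

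**What the plan says.** The Allocation section of the protocol article states: "Randomization was based on a 1:1 ratio and stratified on the baseline HbA1c level (<7.5% vs ≥7.5". It names no other stratification factor. The sequence is permuted in blocks of 2, 4 or 6.

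The Primary outcome analysis section describes the primary model first: "The mixed model will be adjusted for the baseline value of HbA1c, as well as additional baseline variables that might be potential confounders". The additional variables are "center, age, gender, treatment by insulin, duration of diabetes and history of diabetes complications". The same section then covers secondary outcomes. After a bivariate comparison, each is analysed by an ANCOVA "adjusted for the baseline value of the corresponding secondary outcome and the same set of potential baseline confounders than in the primary outcome analysis".

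The Outcomes section lists the between-arm secondary outcomes: nutritional knowledge, dietary intake, physical activity, body composition with BMI and waist circumference, mean glycaemia, blood lipids and quality of life. Study objectives adds HbA1c at 2 years.

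**The concern.** The primary model has two parts: baseline HbA1c, and six further covariates. The secondary ANCOVA has the same shape. The outcome's own baseline takes the first place, and the same further covariates take the second. Baseline HbA1c then drops out of every secondary model whose outcome is not itself HbA1c, and with it the only factor used to stratify the allocation.

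Stratified blocks balance the arms within each HbA1c stratum, so differences between strata contribute almost nothing to the sampling variation of the arm difference. A model without the stratum leaves those differences in its residual. If they matter for the outcome, the model standard error exceeds the true one, the confidence interval is too wide, and the test rejects less often than 5% under the null. Precision that the design has already secured is then not reported.

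**Working it through.** **The plan's own figure.** The sample size fixes the number of patients used below. Inputs from the Sample size section: SD 2, pre/post correlation 0.4, post/post correlation 0.5, 4 post-randomisation measurements, difference 0.5, power 80%, two-sided 5%.

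- Variance factor: (1 + 3 × 0.5)/4 − 0.4² = 0.625 − 0.16 = 0.465.
- n per arm: 2 × (1.960 + 0.842)² × 2² × 0.465 / 0.5² = 116.8, so 117 (234 in all).
- With 20% added: 117 × 1.2 = 140.4, so 141 per arm and 282 in all.

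The stated size is reproduced, and this point does not affect it.

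**Covariates side by side.**

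| Model | Baseline term | Further covariates | Stratification variable included? |
|---|---|---|---|
| Primary mixed model | HbA1c | the six listed | yes |
| Secondary ANCOVA, 2-year HbA1c | HbA1c | the six listed | yes |
| Secondary ANCOVA, other outcomes | the outcome's own | the six listed | no |

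**Size of the error.** The input needed is the partial correlation r between baseline HbA1c and the outcome, given the other covariates. The documents do not give it, so 0.2 to 0.5 is an assumption. The check simulated 234 patients, permuted blocks of 2, 4 or 6 within the two strata, and an assumed truncated-normal baseline HbA1c over about 6.5 to 10%. The ANCOVA was fitted on the outcome's own baseline, with and without HbA1c. The other six covariates were not simulated, so r is to be read as what remains after them.

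| Assumed r with continuous HbA1c | Overstatement of model SE (model SE / true SD, minus 1) | Type I error without HbA1c | Fall in model SE when HbA1c is added |
|---|---|---|---|
| 0.2 | about 0% | 4.8% | 2% |
| 0.3 | about 1% | 4.7% | 5% |
| 0.4 | about 5% | 4.0% | 8% |
| 0.5 | about 8% | 3.8% | 13% |

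Another run of this design, with 6,000 trials per setting, gave overstatements of 1%, 2%, 5% and 8% and type I errors of 4.9%, 4.8%, 3.7% and 3.5%. At 6,000 trials the Monte Carlo error is about √(0.05 × 0.95 / 6000) = 0.3 points on a 5% rejection rate, and about 1/√(2 × 6000) = 0.9% on the SE ratio. Differences of that order between runs are noise.

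**Why the last column is larger.** It follows 1 − √(1 − r²): 2.0%, 4.6%, 8.3% and 13.4%. It combines two effects, which separate in a simulated example at r = 0.4:

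- Without HbA1c, the model SE is 0.1134 against a true SD of 0.1089. The overstatement is 0.1134/0.1089 − 1 = 4.1%.
- With HbA1c, the true SD falls to 0.1048, a real precision gain of 1 − 0.1048/0.1089 = 3.8%.
- The model SE with HbA1c is 0.1039, a total fall of 1 − 0.1039/0.1134 = 8.4%.

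Only the first component is the error from ignoring the stratification.

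**A less favourable assumption.** If r is the partial correlation with the two-level stratum itself, the SE ratio is 1/√(1 − r²) and type I error is 2 × [1 − Φ(1.96 × ratio)]. For r = 0.1 / 0.2 / 0.3 / 0.4 / 0.5 the ratio is 1.005 / 1.021 / 1.048 / 1.091 / 1.155 and type I error 4.9% / 4.5% / 4.0% / 3.2% / 2.4%. These figures are larger because two strata capture only part of the variation in continuous HbA1c. In simulations at 282 patients with r from 0.1 to 0.5, adding the stratum brought type I error to between 4.8% and 5.2%.

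**The case against.** The strongest objection is to the reading. The word used for the six covariates implies that HbA1c may itself count as a confounder, and secondary outcomes are to follow the same principles as the primary. On that view the set carried over already contains HbA1c. The sentence can be stretched this far, but it names HbA1c apart from the list and then puts another baseline in its place. If HbA1c was meant to stay, the sentence still needs to say so.

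A second objection is that the statistical analysis plan, which is not shown, may settle the covariates. That would hold if the article were silent. It states a specific set, and a plan that follows the sentence carries the omission forward.

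A third objection is size, and much of it stands. Insulin treatment and diabetes duration may absorb part of what HbA1c predicts. Nothing in the documents shows that a partial correlation of 0.4 or 0.5 applies to any outcome. The article also makes no power claim for secondary outcomes. A reader might take the 2% to 13% fall in model SE as the error in the planned standard errors. That is not supported, because part of it is the ordinary gain from any prognostic covariate.

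Adjusting for centre, although it was not a stratification factor, is legitimate and no part of this point.

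**Conclusion.** The mismatch between design and analysis is real but modest. On the plain reading, the secondary ANCOVA leaves out the one stratification variable. The standard-error overstatement is negligible at a partial correlation with continuous HbA1c of 0.2 to 0.3, and about 5% to 8% at 0.4 to 0.5. These correlations are assumptions.

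A reader might infer that secondary estimates are biased, that false positives increase, or that every secondary outcome suffers. None of this follows. The estimates are unbiased and the error is conservative. It vanishes for outcomes that HbA1c does not predict, and it does not arise for 2-year HbA1c. The primary mixed model is also unaffected. The case for acting rests on the near-zero cost of the correction, not on the size of the harm.

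**What to change.** In the Primary outcome analysis section, reword the secondary-outcome sentence so that each ANCOVA includes three things: the outcome's own baseline, baseline HbA1c (identified as the randomisation stratification variable), and the six covariates listed for the primary model. For 2-year HbA1c the first two coincide.

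The cost is one phrase and one degree of freedom. Baseline HbA1c must be known for every patient before allocation, so no new data or patients are needed.

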##### Methods for medical-economic analysis

A cost/efficacy ratio will be established:

Differential RCE = Δ Cost between strategies/Δ Efficacy between strategies.

Markovian modelling can be used for the precise estimation of the various costs incurred by the diabetes treatment strategies and the medical repercussions over the 2-year period including published data [20, 21] and expert advice. A sensitivity analysis will be carried out.

#### Data monitoring

A clinical Research associate mandated by the promotor visits regularly each study site and performs all types of site visits including, but not limited to, qualification visits, initiation visits, monitoring visits and termination visits.

During the site visits the CRA will monitor the informed consent, ensure the trial is conducted in compliance with the protocol, ICH/GCP, applicable regulatory requirements and applicable SOPs/work instructions. The CRA will be responsible with trial monitoring on-site of clinical data for accuracy and completeness, and clinical report preparation and presentation.

#### Declaration of serious adverse event

The investigator evaluates each adverse event in terms of its severity.

The pharmacovigilance unit of the Toulouse University Hospital has established a specific form to be completed by the investigator who declares the SAE (serious adverse event) and sends it back.

He must notify the sponsor, without delay from the day of his knowledge, of any serious adverse event from the date of signature of the consent, throughout the duration of the patient’s follow-up planned by the research and up to 8 days after the completion of the participant’s research follow-up, where it is likely to be due to research,

#### Auditing

An audit can be carried out at any time by persons mandated by the promoter and independent of the researchers. Its objective is to ensure the quality of the research, the validity of its results and the respect of the law and the regulations in force.

## Ethics and dissemination

### Regulatory authorizations

All of the authorizations required in accordance with French legislation were obtained for this study: Agence Nationale de Sécurité du Médicament (ANSM) (authorization dated 10/05/2013), Comité Consultatif sur le Traitement de l’Information en matière de Recherche dans le domaine de la Santé (CCTIRS) (Approval Granted on 22/05/2013), Comité de Protection des Personnes (CPP) Sud-Ouest et Outre-Mer (SOOM) (Approval Granted on 27/05/2013), Commission Nationale Informatique et Libertés (CNIL) (Approval Granted on 22/10/2013). This study has been assigned the following numbers: ClinicalTrials No. NCT01955031 and ID-RCB number: 2013-A00391-44.

## Discussion

We hope that the telemonitoring of patients in their own home will lead to new organizational management methods in response to relevant follow-up (consultations not scheduled in advance and appointments made depending on the patients’ state of health). Furthermore, refocusing targets based on the information recorded should have a beneficial impact on patient knowledge, behavior and blood glucose management, preventing diabetic complications in the longer term [22]. Apart from medication, the management of patients with type 2 diabetes is multi-faceted and includes education to promote greater independence, the monitoring of blood glucose levels and changes in lifestyle. It is not easy to change the lifestyle of patients who are set in their ways or to find out more about their physical activities and daily diet. Similarly, it is not easy to sustain the change of attitude needed to control the disease.

Teleeducation tools and connected health devices for telemonitoring purposes can provide both doctors and patients with objective data to discuss optimum solutions on a case-by-case basis. The connected devices per se can be used to teach patients with the support of coaching [23].

We hope that telemonitoring over several months of patients with type 2 diabetes will provide patients with a better understanding of what they need to do to improve blood glucose management and give them the incentive to continue their efforts in the longer term.

Apart from the primary objective concerning blood glucose management, the results of the secondary objectives concerning weight, diet and quality of life should enable us to set targets which are more patient-specific.

The cost-efficacy study will help to establish the economic model to be considered in order to continue this type of activity.

In conclusion, educating patients at home about a balanced diet and physical exercise could be extended to a bigger diabetic cohort if it proves to be cost-effective. Education concerning diet and the introduction of appropriate physical exercise could be used to educate patients with other chronic cardiovascular diseases, obesity or respiratory diseases, etc.

The telemonitoring of chronic diseases is in its beginning. Other studies should highlight patient-specific telemonitoring tools (suitable patients, when, for how long, combination or individual telemonitoring and teleeducation, delegation of tasks and the role of treating physicians, etc.).

## Abbreviations

ANSM: Agence Nationale de Sécurité du Médicament (French National Agency for the Safety of Medicines)
BMI: body mass index
CCTIRS: Comité Consultatif sur le Traitement de l’Information en matière de Recherche dans le domaine de la Santé (French Advisory Committee on Information Processing in Material Research in the Field of Health)
CNIL: Commission Nationale Informatique et Libertés (French National Commission on Data Processing and Liberty)
CPP: Comité de Protection des Personnes–EC (Ethics Committee)
CRA: clinical research assistant
CRF: clinical report form
DQOL: diabetes quality of life
EQ5D: EuroQol five dimensions questionnaire
GPAQ: global physical activity questionnaire
HAS: Haute Autorité de Santé (French Health Authorities)
HbA1c: glycated hemoglobin
ICH/GCP: International Conference on Harmonisation/Good Clinical Practise
ITT: intent to treat
PP: per protocol
SAE: serious adverse event
SOP: standard operating procedure
WHO: World Health Organization
